### Data management

Data entry into the RedCap database will be performed using any device with internet access, allowing for flexible and efficient data collection. To ensure the reliability of the dataset, all entered data will be checked for completeness on a regular basis. The collected data will be accessible to the study team in a pseudonymized and encoded format, maintaining confidentiality and privacy while allowing for effective data analysis. The data manager will back up the dataset at regular intervals, saving it as a CSV file to prevent data loss and ensure the security of the information. Additionally, plausibility checks will be performed to verify the consistency and accuracy of the data. New variables, such as sum scores, will be generated using the statistical software Stata Version 17.0 (59).

The qualitative interviews will be audio-recorded and transcribed for analysis. For transcription, f4x, an online service that complies with the General Data Protection Regulation in Germany (DSGVO) and meets the requirements for medical data, will be used. After transcription, the research staff will review and pseudonymize the transcripts to ensure the confidentiality and the study participants’ personal rights.

### Data analysis

#### Statistical methods

For subproject 1 and subproject 3, we will describe the type, frequency and context of experienced and exerted violence and compare groups by t-test and ANOVAs. Associations will be analyzed by regression and correlation models (60). Further, we consider multilevel models to analyze group-specific association of varying variables with experienced and exerted violence (61, 62). To assess the psychometric characteristics of new developed and translated questionnaires, descriptive analyses and factor analysis will be conducted (60). Finally, we will interpret the qualitative and quantitative data in conjunction and present the results integratively using joint displays (34, 63).

#### Qualitative data analysis

The qualitative data collected in subproject 2 will be analyzed using a hermeneutic-reconstructive methodology to gain deeper insights into the subjective meanings and social contexts within the participants’ narratives. This follows the integrative basic procedure (“Integratives Basisverfahren”) proposed by Kruse (64) and the biographical-analytical approach of Lucius-Höhne and Deppermann (65). Particular attention will be given to the subjective and latent meanings, and the biographical embedding of violence experiences. In addition to the content aspect (factual framework), the sequential text analysis (word-by-word and line-by-line) is carried out at the level of interaction between the interviewer and the interviewee (a), semantics (b), syntax (c) and narrative figures (d), whereby a variety of linguistic-communicative methods, positioning analysis and agency analysis will be applied (64, 65). We aim at the development of case structure hypotheses (“Fallstrukturhypothesen”) and a typology regarding the biographical coping of violence experiences with a special focus on gender and perpetrator-victim dynamics. In line with this, our interpretive analysis will remain attentive to emergent sociocultural themes in participants’ narratives (e.g., migration background, discrimination, family support, religiosity/spirituality) when reconstructing case structures and typologies (66).

This methodological approach is particularly suited to reconstructing case structures in biographical narratives and to capturing the dynamics of victim-perpetrator inversions. To ensure the intersubjective exchange and consensual analysis required for reconstructive analysis, qualitative research workshops will be organized, involving research staff from diverse disciplines and with varying levels of mental health service use experiences.

The qualitative data collected in subproject 3 will be analyzed using qualitative structured content analysis according to Kuckartz (67) and reconstructive analysis according to Kruse (64). For qualitative data management (68) analysis software MAXQDA will be used. In the first step of the content analysis, the transcripts of the first interviews (10–25%) will be coded deductively based on the interview guide topics. Iteratively, the deductive codes and categories will be extended, refined or modified by means of inductive coding. In the second step, the preliminary coding tree will be applied to the entire material and, if necessary, further extended, refined or modified until a final category system is reached.

### Ethics

#### Informed consents

Each potential study participant will be informed verbally and in writing about the study’s aims, procedures, data policies, and potential risks. A copy of the information sheet will be provided to the study participants. After ensuring that they fully understand the study details and all their questions have been answered, informed consent will be obtained separately for each subproject. In subproject 1, participants from the general population will provide informed consent by checking a box at the beginning of the online questionnaire, while patients in psychiatric hospitals will sign an informed consent form. In subproject 2 and subproject 3, participants will send their signed consent form by email or post. Respondents will be assured that they can refuse to participate or withdraw consent at any time without facing any adverse consequences.

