### Participants and eligibility criteria

The standardized survey of subproject 1 includes people with SMI of legal age (18+ in Germany) who are undergoing treatment in one of the participating clinics at the time of recruitment. The term “people with SMI” refers to individuals diagnosed with mental illness that significantly impair their ability to function in daily life. These conditions often include disorders such as schizophrenia, bipolar disorder, or severe major depression, and typically require (long-term) treatment and support (35). For our study, we operationalize the term “people with SMI” based on the indication for psychiatric hospitalization, as well as outpatient treatment in a psychiatric hospital or outpatient service, which is considered an indicator of “severe mental illness”. Synonymously we use the term “mental health service user”. Exclusion criteria include language barriers and cognitive deficits, such as dementia or intellectual disabilities.

The qualitative study of subproject 2 includes persons of legal age who took part in the standardized survey in subproject 1. The selection of participants is based on the extent of violence experienced as indicated in the standardized questionnaire. Participants who report experiences of physical or sexual violence will be considered eligible for the qualitative interviews. The phrase “beyond a cut-off” refers to the self-reported occurrence of at least one experience of physical or sexual violence in the questionnaire. Final selection will additionally consider the forms of violence reported and sociodemographic characteristics in order to ensure heterogeneity of cases.

Individuals who meet these criteria and agree to participate in a narrative-biographical interview will be included. In subproject 3, mental health professionals from the fields of nursing, psychology, social work, and medicine who are employed at one of the participating clinics will be recruited for the qualitative interviews and focus groups, and for the subsequent quantitative survey.

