#### Subproject 3 (qualitative study and quantitative survey with mental health professionals)

To capture both the subjective and collective perspectives of mental health professionals, subproject 3 employs an exploratory sequential design, beginning with qualitative interviews followed by standardized measures. Recruitment takes place at the participating clinics, where staff members from relevant professional groups involved in direct patient care will be invited to take part. For the qualitative study part, we will recruit participants who exhibit a broad range of sociodemographic and professional characteristics (gender, age, professional experience, treatment setting). We anticipate conducting approximately 30 to 40 interviews and about 3 to 4 focus groups. The final sample size will be determined by theoretical saturation. For the following quantitative part, a standardized questionnaire will be administered to assess frequencies and correlations of mental health professionals’ attitudes. Staff members will be invited to participate in an online survey.

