#### Subproject 3 (qualitative study and quantitative survey with mental health professionals)

We collect data on the subjective and collective perspectives of mental health professionals on their client’s violence experiences using qualitative interviews, focus groups, and standardized questionnaires.

Qualitative approach: The guidelines for the interviews and focus groups consist of predominantly open-ended questions about everyday experiences, as well as semi-structured questions to enhance comparability. Data analysis is conducted using content-analytical approaches and supplemented with reconstructive analytical tools. The results are validated through intersubjective exchange and consensus alignment of interpretations during regular participatory research workshops.

Quantitative approach: Based on both the findings from the quantitative survey in subproject 1 and initial qualitative findings in subproject 2 and 3, a questionnaire will be developed to assess and quantify professionals’ perspectives on facilitators and barriers related to dealing with their clients’ experiences of violence. Stigmatizing attitudes will be captured by the German Version of the Community-Attitudes-Toward-the-Mentally-Ill inventory (CAMI) (58).

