#### Confidentiality

Signed consent forms will be kept in a locked file cabinet. Password-protected cloud files will ensure the exchange of information between subprojects. Only collaborating researchers will have access to the stored personal data. Data for analyses will be kept with a cipher and without any personal data. The cipher enables researchers to delete data securely in case of withdraw of consent. The study results will be published anonymously, without the possibility of drawing conclusions about individual participants. Archived data will be archived on servers at the Department of Psychiatry and Psychotherapy at Leipzig University in Germany, and at the Department of Psychiatry and Psychotherapy II at Ulm University in Germany.

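### As written, clinic staff must return a signed consent form to take part in the online stigma survey, so it is not anonymous although nothing in the described analysis needs identity

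*Protocol article*

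**What the plan says.** The Informed consents section first sets the unit of consent: "informed consent will be obtained separately for each subproject". Within subproject 1 it distinguishes two routes. Patients sign a form, whereas "participants from the general population will provide informed consent by checking a box at the beginning of the online questionnaire". For the other two subprojects it gives a single route: "In subproject 2 and subproject 3, participants will send their signed consent form by email or post".

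Subproject 3 has several components. Study design lists interviews, four focus groups and then quantitative data from about 100 professionals. Participants and eligibility criteria says that professionals "who are employed at one of the participating clinics will be recruited for the qualitative interviews and focus groups, and for the subsequent quantitative survey". The recruitment section for subproject 3 gives the mode: "Staff members will be invited to participate in an online survey". The instruments section for subproject 3 gives the sensitive content: "Stigmatizing attitudes will be captured by the German Version of the Community-Attitudes-Toward-the-Mentally-Ill inventory (CAMI").

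The Confidentiality section says that signed forms are locked away, that only researchers on the project can reach personal data, and that analysis data carry a cipher in place of personal data. It adds that the cipher lets the team delete a person's data after withdrawal. It also states: "Archived data will be archived on servers at the Department of Psychiatry and Psychotherapy at Leipzig University", with a second archive at Ulm. The psychiatric clinic of the University Hospital of Leipzig is one of the recruiting sites.

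**The concern.** The staff survey asks employees about their attitudes to people with mental illness and about barriers to dealing with clients' experiences of violence. The Introduction cites an Australian study in which some professionals played down or blamed disclosures of sexual assault, so candid answers may be unflattering. A respondent who has signed and returned a form knows that the research team can identify them, however well the form is stored. That knowledge can shift answers towards what is acceptable, on the very construct being measured.

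A signed form sent separately from an online questionnaire is also an extra step at which willing staff can drop out.

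At stake is the credibility of the stigma and barrier results, which are central to subproject 3. A larger sample would not repair a shift in how people answer.

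**Working it through.** The protocol states no figure on this point, so the check is mainly a reading of passages side by side.

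**1. Does the signed-form rule reach the online survey?**
- The rule covers participants in subproject 3 (Informed consents).
- Survey respondents are subproject 3 participants (Study design; Participants and eligibility criteria; the subproject 3 recruitment section).
- No exception is stated. The same section does separate routes within subproject 1, where the online sample "will provide informed consent by checking a box at the beginning of the online questionnaire" and patients sign.
- Result: read literally, yes.

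**2. Are the answers named, pseudonymous or anonymous?**
- Names sit on locked consent forms and analysis data hold no personal data, so the answers are not named.
- The cipher permits deletion of one person's data on withdrawal, which is possible only if person and record can be linked. The answers are therefore not anonymous either.
- Result: pseudonymous, and identifiable to the research team.

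**3. Does anything described need the link?**
- Promotion of study participation pays the 30 euro incentive for the qualitative parts only.
- The survey is described as a single administration with no follow-up.
- The planned comparison of professionals' views with those of service users (Outcomes, subproject 3) needs no individual linkage.
- Result: the only stated use is deletion on withdrawal.

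**4. Can the effect be sized?**
- The document gives no expected response rate and no effect of identifiability on the attitude scale, so the effect cannot be derived.
- For scale only, the 95% half-width for a proportion of 50% at n = 100 is 1.96 × √(0.25/100) = 0.098, or 9.8 percentage points.
- Suppose, purely as an assumption, that 40% would endorse a stigmatizing answer anonymously and that 10% to 25% of these would not do so when identifiable. The observed figure would be 0.40 × 0.90 = 36% down to 0.40 × 0.75 = 30%, a shift of 4 to 10 points.
- The range follows entirely from the assumed inputs. It shows what such a shift would look like beside sampling error and is not an estimate for this survey.

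**The case against.** The strongest reply is that a condensed article summarises consent by subproject in one sentence, probably with the interviews and focus groups in mind. Participant timeline shows interviews well advanced and the survey still ahead, planned for October to December 2025. That may be the intention. If so, the correction is a clarification. The text nevertheless states a positive rule without exception, and following it would produce the problem, so this is more than an omitted detail.

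The safeguards in the Confidentiality section are real. A reader might infer that the survey is answered by named employees. The document does not support that, because names and answers are held apart. What remains is identifiability to the team.

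The employer link is also limited. The article does not say who receives the staff forms, and Leipzig is one recruiting clinic among several. The link between an archiving department and a recruiting clinic is stated for that site and should not be extended to the whole survey.

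A reader might also treat the absence of a social desirability scale for staff as an error, since subproject 1 has one. The staff questionnaire was still to be developed and the article does not claim a complete instrument list, so this is not a finding.

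Finally, anonymity has a price: the assurance that consent can be withdrawn at any time could not be honoured by deleting answers once they are submitted. This stands as a genuine trade-off.

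**Conclusion.** The point holds as a cheap improvement to the design. As written, staff must return a signed form for an online survey on stigmatizing attitudes. The other online survey in the protocol uses a tick box, and the only stated purpose served by an identity link is deletion on withdrawal. This creates a risk of socially desirable answers and of lower response.

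Two stronger readings are not supported. The first is that stigma estimates will be biased downwards. Under-reporting is the plausible direction for socially desirable answering, but the document neither shows nor sizes it. Non-response could act in either direction, since staff may fail to return a form merely for lack of time. The second is that the sample will shrink well below 100. The figure of about 100 describes data collected, so forms not returned would first mean inviting more staff.

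The conclusion rests on a literal reading of the consent rule and on the general cipher wording applying to the staff survey.

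**What to change.** In Informed consents, limit signed forms in subproject 3 to interviews and focus groups. For the staff online survey, use tick-box consent on the opening page and collect no name, email address or cipher link. If earlier participation in an interview or focus group matters for the analysis, ask it as a yes/no item.

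Two further passages need matching changes. The withdrawal assurance in Informed consents and the cipher-deletion statement in Confidentiality should both say that anonymous survey answers cannot be removed once submitted. The survey's information page should say the same.

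The cost is a few sentences and a notification through the route given under Protocol amendments. The downside is the loss of deletion after submission, which is small for a single questionnaire if respondents are told beforehand.

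If the survey has already run with signed forms, the consent route cannot be changed. The report should then state that respondents were identifiable to the research team and discuss this as a limitation of the attitude results and of response.

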#### Confidentiality

Signed consent forms will be kept in a locked file cabinet. Password-protected cloud files will ensure the exchange of information between subprojects. Only collaborating researchers will have access to the stored personal data. Data for analyses will be kept with a cipher and without any personal data. The cipher enables researchers to delete data securely in case of withdraw of consent. The study results will be published anonymously, without the possibility of drawing conclusions about individual participants. Archived data will be archived on servers at the Department of Psychiatry and Psychotherapy at Leipzig University in Germany, and at the Department of Psychiatry and Psychotherapy II at Ulm University in Germany.

#### Harms

As this is an observational study without an intervention, we do not expect adverse events. The study team is prepared and trained to provide tools to help study participants in case of emotional reactions, like dissociation, to remembering challenging life events like experienced and exerted violence. The evaluation team will be trained and provided with structured instructions to recognize and deal with suspicions or statements of suicide of the participants. Researchers will be in regular exchange of information; any reported adverse event will be documented and discussed. In the unlikely case of an adverse event, it will be documented in an encrypted file.

#### Auditing

No external auditing will be provided. The study progress will be discussed in weekly meetings of the research team. Materials including interview guides and questionnaires will be discussed with experienced experts and in research workshops.

#### Protocol amendments

Important changes to the protocol will be submitted to the responsible ethics committee. Changes are updated in the German Clinical Trials Register (69).

## Discussion

Globally, victimization is recognized as one of the pressing problems in the treatment and care of people with SMI (70). Victimization has serious consequences for mental health, leading to poor clinical outcomes and hindering recovery in an already vulnerable group (70–75). To date, effective measures to prevent and reduce victimization among this group are widely lacking. This is in stark contrast to the right to protection from all forms of exploitation, violence and abuse, including gender-based violence, as well as the corresponding obligation to take appropriate measures, as declared in Article 16 of the UN Convention on the Rights of Persons with Disabilities (76). The low awareness and lack of interventions against victimization in mental health treatment and care further contradict the core principles of social psychiatry, which emphasize the significant role of social and biographical factors in the treatment and care of mental health service users. The development of successful preventive measures requires a comprehensive understanding of victimization. With our mixed-methods study, we aim to address several research gaps:

Although internationally established findings exist regarding the increased risk of victimization among people with SMI and the severe consequences for mental health and recovery processes, there is a scarcity of empirical data in Germany concerning the prevalences and forms of physical or sexual violence experiences among this group. The transferability of findings from international studies is limited due to differences in socio-cultural factors and structures of healthcare systems.The prevalence rates of victimization among people with SMI reveal striking gender differences compared to the general population. We aim to explore the significance of gender in experiences of violence within both heterosocial and homosocial contexts, drawing on socio-cultural and socio-structural gender theories that frame violence as an expression of status positions.Since violence experiences among people with SMI often exhibit an overlap between victimization and perpetration of violence, we aim to gain insights beyond rigid attributions of (male) perpetrator status versus (female) victim status, and we shed light on the forms and mechanisms of perpetrator-victim-overlaps. This approach seeks to undermine a dichotomous understanding of people with SMI as either victims or perpetrators.Quantitative studies provide limited insights into the complexity of violence experiences. Due to the temporal structure of violence experiences, we investigate experiences of violence through a biographical approach, which appears particularly suitable for investigating serial or re-victimization as well as biographical continuities, disruptions, and transformations in the violence experiences.There are only a few studies on the perceptions, considerations, and the therapeutic management of mental health service users who experienced violence, as well as on the support needs of psychiatric professionals in dealing with their clients’ violence experiences. By investigating perspectives of mental health professionals in dealing with service users’ experienced violence and their disclosure, we aim to gain insights into how mental health professionals’ attitudes impact the opportunities for disclosing violence experiences in psychiatric settings.

Our study aims to contribute fundamentally to a deeper understanding of violence experienced by people with SMI in Germany, thereby providing the groundwork for the development of targeted interventions to improve awareness and the response to such experiences within this particularly vulnerable group.
